### Interventions and procedures

Eligible participant dyads will be randomized in equal proportions between a group receiving usual care and a group receiving the FindMyApps intervention.

#### FindMyApps intervention

Those participants receiving the FindMyApps intervention will receive training in the use of FindMyApps and will have access to a tablet (either an iPad running the iOS operating system or an alternative model running the Android operating system), on which the FindMyApps app is installed. The tablet may belong to the participants or be provided as part of the intervention. We outline below the FindMyApps intervention. For further details we refer readers to the published literature [26–28].

The FindMyApps app is a selection tool designed to help people with early stage dementia or MCI, if needed with support of a caregiver, find apps for self-management and meaningful activities that fit their needs, wishes and abilities [26].

The FindMyApps selection tool consists of a native app with a specially designed user interface and a cloud-hosted database of apps that have been assessed as meeting essential criteria for usability by people with dementia and MCI [28].

The user interface consists of several pages:
a page for setting the user-profile, whereby the users are invited to answer some questions on their preferences, needs and abilities, such as letter size, and language preferences;a series of pages where users can search for apps for self-management and meaningful activities, within three main categories (‘In and around the house’, ‘Social Contact’ and ‘Free Time activities’), each of which is divided into a range of subcategories;pages containing more detailed information about individual apps and the extent to which they meet the user’s specified preferences, with links to the app store to allow the user to download the app;a page (MyApps) which provides an overview of apps previously viewed in the app store (iOS) or apps already downloaded by the user (Android); anda page on which videos providing instructions in the use of the tablet and the FindMyApps app can be viewed.

At the beginning of the intervention period, participants will receive a brief written guide to the general use of their tablet. This will be sent by email or post, dependent on the participant’s preference. The videoconferencing software Microsoft Teams will be used for an initial videocall, during which a member of the research team will expand on the content of this brief written guide with further verbal explanations and instructions. The researcher will encourage the caregiver to demonstrate functions of the tablet to the person with dementia (turning the device on and off, charging the device, changing the volume, navigating the home screen, and starting and exiting applications). During the same call, participants will be talked through the installation and initial set-up of the FindMyApps app by the researchers. Using the Microsoft Teams screen-sharing functionality, the researcher will use pre-installed system apps and the FindMyApps app on a device comparable to the model used by the participant to demonstrate how to navigate within apps and how to operate settings within apps. Participants will have the opportunity to view a short instruction film that outlines the functions of the FindMyApps app. This film was scripted by the researchers and produced by the media team at GGZ InGeest/VUmc for the FindMyApps study. Using the Microsoft Teams screen-sharing functionality, participants will have the opportunity to practice operating the tablet and the FindMyApps app, with support from the caregiver and researcher as required. The duration of this entire meeting is expected to be 45–60 min.

The caregiver of the participant dyad will receive a written guide describing the ‘Errorless learning’ method and explaining how they can use this approach to further support the person with dementia to learn to use the tablet and the FindMyApps app. The ‘Errorless Learning’ method, which has been demonstrated to be an effective method for facilitating learning of new skills by people with cognitive impairment [33]. The technique focuses on learning through the strengthening of procedural memory, by allowing a person to practice a routine or sequence of steps, with errors immediately corrected by a facilitator. This guide will be sent by post or by email, depending on the participant’s preference. The contents of the guide will be further discussed, with additional verbal explanations provided by one of the researchers, during a telephone call or videocall using the software Microsoft Teams.

During the 3 months intervention period, participating dyads are advised to use the tablet together, in 7 follow-up sessions (of recommended duration 30–45 min), during which the caregiver applies the errorless learning method to train the participant in using the tablet and the FindMyApps app. After these training sessions the participants are expected to be able to use some apps independently and use the FindMyApps app, either with some help or independently. Previous pilot studies showed that downloading new apps often still requires guidance from the caregiver, even after the training sessions [33]. Participants are free to use the tablet and associated apps as much or as little as they choose.

Participants have access to both of the previously described training films through the FindMyApps app, which they can watch at any time to review the instructions received in the first face-to-face meeting. Participants are also provided with contact details by which they can consult a helpdesk run by EUMediaNet (the technical developer of the FindMyApps app), in case of questions or problems with the tablet or apps.

#### Usual care

Those receiving usual care will have access to a tablet; either an iPad running the iOS operating system or an alternative model running the Android operating system. The tablet may belong to the participants or be provided by the researchers.

At the start of the intervention period, the participants will be provided with a brief written guide to the general use of their tablet and a list of websites from which they can learn more and find suggestions for useful and user-friendly apps. This will be sent by email or post, dependent on the participant’s preference. The videoconferencing software Microsoft Teams will be used for an initial videocall, during which a member of the research team will expand on the content of this brief written guide with further verbal explanations and instructions. The researcher will encourage the caregiver to demonstrate functions of the tablet to the person with dementia (turning the device on and off, charging the device, changing the volume, navigating the home screen, and starting and exiting applications). Using the Microsoft Teams screen-sharing functionality, the researcher will use pre-installed system apps on a device comparable to the model used by the participant to demonstrate how to navigate within apps and how to operate settings within apps. Using the Microsoft Teams screen-sharing functionality, participants will have the opportunity to practice operating the tablet, with support from the researcher as required. The duration of this entire meeting is expected to be 45–60 min.

During the 3 months intervention period, participant dyads are advised to use the tablet together, so that the person with dementia/MCI can learn with support from the caregiver. Participants are provided with a link to a video, which they can watch at any time to review the instructions received in the first face-to-face meeting. This instruction film was scripted and designed by the researchers and produced by EUMediaNet for the FindMyApps study. Participants are also provided with contact details by which they can consult the study helpdesk.

### Potential harms

As a non-clinical psychosocial intervention, and on the basis of earlier feasibility and pilot studies evaluating FindMyApps, we do not anticipate that subjects are likely to experience severe adverse events.

Nonetheless, study participants are advised to contact researchers at any time with any problems or adverse events, which will be logged by researchers. Researchers have contact with participants approximately every four weeks during the study (to collect intermediate app use and care use data – see Fig. 1), at which points participants are also asked about any adverse events. Logs of reported problems or adverse events will be reviewed on a regular basis and any appropriate follow-up action taken.

**Fig. 1 Fig1:**
[figure not shown]
Trial flowchart

Special consideration will be given to avoiding and mitigating participants’ risk of exposure to the 2019-nCoV coronavirus through their participation in the study. After an initial suspension of the study, this protocol was updated on 14-05-2020, based on national guidelines to ensure the safety of participants [34]. By default, information letters and handouts will be sent to participants digitally and consent will be recorded by participants digitally, in line with guidance received from the medical ethics committee of VUmc. As such, the only remaining physical component of the intervention or method (thus representing the only increased risk to participants as a result of participation in the research) is the loaning of tablets owned by the research group to those participants who do not own a tablet.

Current advice from the World Health Organization is that the 2019-nCoV coronavirus can remain potentially infectious on surfaces for up to 72 h on plastics and stainless steel, and less than 24 h on cardboard [35]. Surface cleaning with common household products is believed to be perfectly sufficient to fully decontaminate them.

Measures will be put in place to further mitigate the risks associated with the loaning of tablets to participants. The number of members of the research team handling the tablets will be kept to a minimum. Those members of the research team handling tablets will immediately report any symptoms suggestive of COVID-19 infection and will immediately stop handling the tablets for a minimum period of two weeks.

Immediately prior to delivery of the tablet to the participant, the tablet, charging cable, box and any other physical components will be cleaned with disinfectant wipes. Tablets will be delivered to the participant’s home either by courier service or one of the research team (observing all protective public health measures), depending on what is logistically feasible. Participants will be advised not to remove the tablet from the box or handle the box for at least three days after it is delivered. If they do handle the box, when first receiving the delivery for example, they should wash their hands immediately afterwards, and before touching anything else, with soap and warm water.

At the end of the intervention period, tablets will only be collected from participants who report that they have been free of symptoms associated with COVID-19 infection for at least 14 days. Arrangements will be made for tablets to be collected either by courier service or one of the research team (observing all protective public health measures), depending on what is logistically feasible. On receipt of the tablet by the research team, the tablets and all associated components will be immediately cleaned with disinfectant wipes. No tablet will be loaned out to a new participant, within 7 days of collection from a previous participant.

### Outcomes

All primary and secondary outcomes will be assessed after three months, compared to baseline.

#### Primary outcomes

Person with dementia/MCI: Self-management; social participation; Caregiver: Sense of competence.

#### Secondary outcomes

Person with dementia/MCI: Experienced autonomy; quality of life (health related); neuropsychiatric symptoms.

Caregiver: Attitudes towards dementia; experience of providing care; quality of life (health related).

### Participant timeline

Figure 2 provides an overview of the time points in the study, and which data are collected and interventions delivered at each time point. Baseline measurements will be completed via online and telephone questionnaires within 7–14 days of group allocation. The first videocalls for initial set-up of the tablet and training in the use of the tablet will normally follow within 7 days of baseline measurements, and in any case will take place within 14 days of the baseline measurement.

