## Trial design

This is a randomized, controlled, non-blinded superiority trial with two parallel groups and two measurements (before the start of the intervention and after three months).

Alongside the effectiveness evaluation, a cost-effectiveness analysis and a process evaluation will be carried out.

The trial is registered in the Netherlands Trial Register: NL8157.

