### Blinding

Due to the nature of the intervention, it is not possible to blind study participants, caregivers or interviewers to the allocation status of participants and outcome measures in the study are based on participant and caregiver self-report. Efforts will be made by researchers to minimize the awareness of participants in the control group of the nature of the FindMyApps intervention. In communication by researchers with study participants, the emphasis will be placed on the evaluation of the effect of the use of tablets and apps, rather than on the evaluation of FindMyApps per se. Through these measures, it is probable that participants will remain blind to the hypotheses being tested.

Data analysis will be conducted by researchers blinded to the group identities. Independent researchers with a data management role will remove or replace identifiers from the datasets prior to analysis, namely the participant codes and the labels of the group variable.

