### Data management and analysis

Quantitative demographic data and data pertaining to participants who withdrew from the study after randomization (dropouts) will be analyzed with descriptive statistics. Differences between the trial arms will be tested with appropriate (non) parametric differences tests (Chi2, Mann-Whitney U, Student’s t-test).

For the effect evaluation, differences between the groups on the primary outcome measures will be tested by MANCOVA on post-test data, including baseline data and potential confounders as covariates in the analysis. Diagnosis (MCI or dementia) will be included as a fixed factor. We will carry out both intention-to-treat and ‘per protocol’ analyses following completion of data collection. Where we encounter missing data as a result of participants withdrawing from the study, we will use appropriate methods to impute that data and perform sensitivity analyses accordingly. Analyses will be conducted using SPSS. We will primarily report effect sizes with calculated 95% confidence intervals, however we will also report *p*-values. We will use 2-tailed p-values with an alpha of 0.05.

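### Baseline follows group allocation in an unblinded trial, so the covariate in the primary MANCOVA may be affected by knowledge of the arm

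*Protocol article*

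**What the plan says.** Four statements in the protocol article bear on this point.

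- **Participant timeline:** "Baseline measurements will be completed via online and telephone questionnaires within 7–14 days of group allocation". The first training videocalls "will normally follow within 7 days of baseline measurements, and in any case will take place within 14 days of the baseline measurement".
- **Trial design:** the first of the two measurements is promised before the intervention starts. Nothing is said about its being before randomization.
- **Blinding:** "it is not possible to blind study participants, caregivers or interviewers to the allocation status of participants". The same sentence adds that the outcomes rest on what both members of the dyad report themselves. Two safeguards are described. Communication with participants plays down FindMyApps as the object of study, and the data analysts are blinded to group.
- **Data management and analysis:** the primary outcomes are tested by "MANCOVA on post-test data, including baseline data and potential confounders as covariates in the analysis".

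Under Data collection methods, trained researchers complete the questionnaires of the person with dementia during an interview. Caregivers by default complete theirs online.

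**The concern.** Randomization makes a baseline covariate safe to adjust for because a value recorded before allocation cannot depend on the arm. Here the value is recorded after allocation, from self-report. For the person with dementia it is taken by an interviewer who, according to the article, cannot be blinded. If either party knows the arm at that moment, expectation or scoring habit can move the baseline mean in one arm. The MANCOVA would treat that movement as a chance imbalance and correct the treatment effect for something that was never a true difference between the arms.

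At stake are the adjusted estimate on the primary outcomes and the error rate of their test. The problem cannot be repaired for a dyad once its baseline has been collected in this order.

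**Working it through.** **1. Does baseline come after allocation?** The phrase used for the interval does not itself say before or after, so try both readings against the videocall window.

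- *Baseline before allocation:* put baseline at day 0 and allocation at day 7 to 14. The videocall normally falls by day 7, which is on or before allocation. Even the outer limit of day 14 leaves only 0 to 7 days after allocation. The call includes installation of FindMyApps in one arm and not in the other (FindMyApps intervention and Usual care sections), so it cannot normally precede allocation.
- *Baseline after allocation:* allocation, baseline within 7 to 14 days, videocall within 7 and at most 14 days after that. Everything fits, and it agrees with the Trial design section.

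The second reading is the one the text supports.

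**2. Does anything keep the arm hidden at baseline?** Analyst blinding acts after the data exist. Playing down FindMyApps acts on participants' expectations and does not touch the interviewer. No section says that allocation is withheld until baseline is complete.

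**3. The plan's own figure.** The Sample size section gives a total of 158 (two outcomes, two groups, alpha 0.05, power 0.80, moderate effect). With a noncentral F, df1 = 2, df2 = N − 3, noncentrality N × f² and f² = 0.0625, N = 158 gives power 0.802, so the figure reproduces. It does not depend on the timing of baseline and is unaffected by this point.

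**4. Size of the possible bias.** Let knowledge of the arm shift the between-arm difference by s0 at baseline and s1 at follow-up, in SD units, and let b be the within-arm slope of follow-up on baseline. The adjusted difference is the true effect plus s1 minus b × s0, so

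bias = s1 − b × s0.

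- Shift at baseline only (s0 = s, s1 = 0): bias = −b × s.
- Same shift at both times (s0 = s1 = s): bias = s(1 − b). With a clean pre-allocation baseline it would be s.

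The documents give neither s nor b. Assumed ranges:

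| s | baseline only, b = 0.5 | baseline only, b = 0.7 | persists, b = 0.5 | persists, b = 0.7 |
|---|---|---|---|---|
| 0.1 | −0.05 | −0.07 | +0.05 | +0.03 |
| 0.2 | −0.10 | −0.14 | +0.10 | +0.06 |
| 0.3 | −0.15 | −0.21 | +0.15 | +0.09 |

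A negative s reverses every sign.

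**5. Effect on the test.** A two-outcome MANCOVA was simulated with no true effect, N = 150 and 4000 runs per setting. The outcomes were assumed correlated 0.3, and the shift was applied to both outcomes at baseline only, in one arm. The simulated biases matched −b × s. Rejection rates at a nominal 5%:

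| s | b = 0.5 | b = 0.7 |
|---|---|---|
| 0 | 5.0% | 4.8% |
| 0.1 | 6.1% | 9.6% |
| 0.2 | 10.8% | 23.6% |
| 0.3 | 19.3% | 46.8% |

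At N = 120 (150 less 20% dropout) the rates for s = 0.1, 0.2 and 0.3 were about 6–8%, 10–19% and 16–40%.

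**The case against.** The strongest reply is that the premise is inferred. The article says that blinding is impossible because of the nature of the intervention. It does not say when the dyad or the baseline interviewer learns the arm. The flowchart and the timeline figure are not shown, and the article condenses a longer protocol. There is also real mitigation: "Through these measures, it is probable that participants will remain blind to the hypotheses being tested". Controls receive a tablet, a guide, a call of the same expected length, a film and a helpdesk, and every participant is offered FindMyApps after the trial. The PAL and MSPP ask about what was actually done, which is plausibly less open to expectation than attitude items. The caregiver outcome is by default completed without an interviewer.

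Much of this stands, and it limits the point to a risk. It does not remove it. Hypothesis masking covers participants and not interviewers, and the order of steps is a stated procedure rather than a detail left to another document.

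Three stronger readings are tempting and are not supported:

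- *The primary estimate is biased by a known amount.* The time of disclosure is not given, and both s and b are assumed.
- *The bias always works against FindMyApps.* That needs an upward shift in the FindMyApps arm (or a downward one in controls) confined to baseline. Follow-up is unblinded too. If the same shift persists, the bias takes the sign of s, and adjustment makes it smaller than a clean baseline would. The error rates above also hold only for a shift confined to baseline.
- *Disappointed controls leave before baseline and spoil the intention-to-treat set.* Nothing in the text points to such withdrawals. The analysis section already plans an intention-to-treat analysis, imputation for dyads who withdraw, and sensitivity analyses.

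**Conclusion.** The point holds as a risk of bias. That baseline follows allocation is well supported by the Participant timeline section. That the covariate in the primary analysis is left unprotected follows from the Blinding and analysis sections. Whether a shift occurs, how large it is and which way it goes cannot be derived from the documents.

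Under the assumed ranges the adjusted effect would be off by 0.05 to 0.21 SD, opposite in sign to the shift, if only baseline is affected. It would be off by 0.03 to 0.15 SD, in the direction of the shift, if the shift persists unchanged. With no shift the planned test keeps its 5% error rate. The case for acting is that the exposure concerns the primary outcomes and is cheap to close beforehand.

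**What to change.** 1. **Preferred.** Complete and lock the baseline questionnaires of both dyad members in Castor before randomization is executed, and randomize soon afterwards. Re-word the Participant timeline section to say so.
2. **Change the videocall window in the same edit.** It is now counted from baseline. Merely turning the present interval into 7 to 14 days before allocation would put the normal videocall on or before allocation. The window should be restated so that it falls after allocation, for example by counting it from allocation, with a length set by the sponsor.
3. **If allocation must come first,** state that it is concealed from the dyad and from the baseline interviewer until the baseline form is locked.
4. **For dyads already randomized in the present order,** add a sensitivity analysis without adjustment for the post-allocation baseline, and read it beside the adjusted one. It is free of a shift confined to baseline, but it carries a persisting shift in full.

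Cost: revised wording and a re-ordered Castor workflow, with no extra visits or participants. A few dyads may complete baseline and then not be randomized. The unadjusted analysis is less precise. With equal variances at both times its standard error is larger by a factor of 1/√(1 − b²), which is 1/√0.75 = 1.15 for b = 0.5 and 1/√0.51 = 1.40 for b = 0.7.
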